# Iron-fortified lentils to improve iron (Fe) status among adolescent girls in Bangladesh - study protocol for a double-blind community-based randomized controlled trial

**DOI:** 10.1186/s13063-019-3309-4

**Published:** 2019-05-02

**Keywords:** Micronutrient deficiency, Iron (Fe), Food-based approach, Food technology, Fortification

## Abstract

**Background:**

Lentils are generally considered to be a nutrient-dense food, and a good source of iron (Fe). This study aims to establish novel evidence of the effectiveness of the consumption of Fe-fortified lentils in improving the body Fe status and thus cognitive performance in non-pregnant adolescent girls in rural Bangladesh, compared to consumption of ordinary lentils.

**Methods:**

We have designed a double-blind (both trial participants and outcome assessors), community-based, cluster-randomized controlled trial among 1260 Bangladeshi adolescent girls between the ages of 10–17 years who are non-smoking, not married, not pregnant, not breastfeeding, and generally healthy at the time of enrollment. The intervention will include three arms who will receive: (1) Fe-fortified lentils; (2) unfortified lentils; or (3) usual intake. Participants will be served a thick preparation of cooked Fe-fortified lentils (37.5 g raw lentils, approximately 200 g cooked lentils) 5 days per week for 85 feeding days (around 4 months) using a locally acceptable recipe. Lentils were fortified with Fe in the laboratory at the Department of Plant Sciences at the University of Saskatchewan in Canada. A subsample of participants (*n* = 360) will be randomly invited to be included in cognitive testing.

**Discussion:**

Data on socio-demographic characteristics, household food security status, adolescent food habits and cognitive testing will be collected at baseline and endline (4 months). Venous blood samples will be collected at baseline, midline (2 months) and endline to measure adolescents’ Fe status. Computerized cognitive testing will include five common measures of attentional (three of attention) and mnemonic functioning (two of memory) carried out using DMDX software. The results of this study will be used to garner support for and to substantiate large-scale production and market expansion of Fe-fortified lentils, and will contribute to knowledge about how to enhance Fe status in adolescents worldwide in resource-poor settings, using staple food crops.

**Trial registration:**

ClinicalTrials.gov NCT03516734. Registered on 24 May 2018.

**Electronic supplementary material:**

The online version of this article (10.1186/s13063-019-3309-4) contains supplementary material, which is available to authorized users.

## Background

Based on data from 2011 to 2012, it was estimated that 26% of non-pregnant non-lactating (NPNL) women and 17.1% of adolescents aged 12–14 years were anemic (< 12.0 g/dl) in Bangladesh, and that prevalence was higher in rural areas [1]. National levels of the reported prevalence of iron deficiency anemia in children aged 6–11 years (hemoglobin < 11.5 g/dl and ferritin < 15.0 μg/L) was 1.3% and in adolescents aged 12–14 years (hemoglobin < 12.0 g/dL and ferritin < 15.0 μg/L) it was 1.8% [2]. Adolescents girls are particularly vulnerable to iron (Fe) deficiency with and without anemia due to their significant growth and development, lifestyle and food habits, and their regular menstrual losses of Fe [3, 4].

Improving dietary Fe intake via Fe supplementation or high-Fe foods is extremely important among adolescent girls living in Bangladesh and other resource-poor settings, in order to maintain nutrition status and growth. Food-based approaches such as Fe fortification have the potential to be sustainable in meeting the increasing demand for Fe among adolescent girls, whereas direct Fe supplementation is often a problem due to poor compliance [5, 6]. Lentils (locally known as *masur dal* in Bangladesh) are a nutrient-dense staple in South Asia, and a good source of Fe. There has been great progress made in lentil fortification and biofortification research over the past decade [7–9]. Lentils grown in Saskatchewan, Canada are rich in Fe (73–90 mg/kg), zinc (Zn, 44–54 mg/kg), and selenium (425–673 μg/kg) [7, 10]. Further research has shown that Saskatchewan-grown lentils are also naturally lower in phytic acid (2.5–4.4 mg/g), indicating that Fe and Zn would be more bioavailable [7, 10–12]. Furthermore, Fe status is associated with improved cognitive performance [13, 14]. Therefore, there is a tremendous opportunity to include lentils as part of a whole-food-based, sustainable solution to the global micronutrient deficiency problem. This community-based trial is designed to examine the effectiveness of Saskatchewan-grown Fe-fortified lentils in improving the Fe status and cognitive performance of adolescent girls in Bangladesh.

## Trial objectives

The primary objective of the study is to determine the effectiveness of an Fe-fortified lentil-based dietary intervention compared to ordinary lentils and usual intake group in improving the Fe status of non-pregnant adolescent girls in Bangladesh. The primary comparison would be Fe-fortified lentils versus non-Fe-fortified lentils and the secondary comparison would be Fe-fortified lentils versus usual intake. We hypothesize that the supplemental food-based Fe from the fortified lentils will improve body Fe status in adolescent girls, and thus cognitive performance, compared to ordinary lentils and usual intake. Furthermore, we will examine the effect of Fe-fortified and non-Fe-fortified Canadian lentil consumption (intervention) on growth (height, body weight, triceps skinfolds, mid-upper arm circumference) of non-pregnant adolescent girls in Bangladesh.

## Material and methods

### Feasibility study

Before designing the effectiveness trial, a feasibility study was conducted in Bangladesh in 2017 to examine the logistics and feasibility of the implementation of a human food intake trial of Fe-fortified lentils among adolescent girls (10–17 years) for 12 weeks [15]. The purpose of the study was to determine the viability of the proposed effectiveness trial. Both thin and thick traditional lentil dishes were prepared based on uncooked/raw lentil amounts of 25 g, 37.5 g, and 50 g/person [15]. The study findings suggested that adolescents were keen to eat cooked lentils over the 3-month study period, and the drop-out rate was 0% (with 5.2% of meal missed by participants). Adolescents’ hunger, fullness, and gastrointestinal discomfort before and after consuming cooked lentil portions were assessed using a visual analog scale (VAS). Higher palatability was observed for the thick preparation of cooked lentils compared to the thin preparation for all three intervention raw amounts of 25 g vs 37.5 g vs 50 g (cooked amount ~ 157.9 g vs 202.7 g vs 256.6 g, respectively). There were no significant differences between uneaten amounts of the lentil dishes containing 37.5 g vs 50 g raw lentils (cooked amount ~ 202.7 g vs 256.6 g, respectively). Moreover, 37.5 g raw amount would provide approximately 86.3% and 46% of the recommended dietary allowance (RDA) for Fe for adolescent girls aged 9–13 and 14–18 years, respectively [15]. Considering the cultural appropriateness of the amount of cooked lentil (*dal*) consumed and its Fe content, the study adopted 37.5 g raw lentil (~ 200 g cooked amount) as the intervention portion size for the future human effectiveness trial.

### Study design

This manuscript describes the protocol for a double-blind (both the trial participants and the outcome assessors), community-based, cluster-randomized controlled trial designed to test the effectiveness of consuming Fe-fortified lentils to improve Fe stores and cognitive performance (attention, and memory) in adolescent girls in rural Bangladesh. Given the context of this problem, the cluster-randomized controlled trial allows us to (1) avoid confounding and ensure representativeness at baseline; (2) minimize risk of contamination between treatment arms; and (3) examine the temporal relationship between our intervention and the outcome.

### Study settings and target population

The effectiveness study will be conducted at the BRAC Adolescent Clubs [16]. These clubs target all adolescent boys and girls in the community, regardless of their school attendance, marital status, or socio-economic status. The clubs provide a unique opportunity for adolescents to socialize in both rural and urban settings. Each club has a membership of 25–40 adolescent boys and girls aged 10–19 years. The clubs operate in the afternoons in BRAC school environments. In the absence of such facilities, a room is rented locally by BRAC. The clubs have various activities to encourage the participation of adolescent girls and boys such as life-skill-based education (LSBE) sessions, access to mini-library facilities, cultural activities, and sports. BRAC provides all materials related to these activities, e.g., books, magazines, and games equipment. The clubs will be selected from four subdistricts (*Upazilas*) i.e., Muktagacha, Nanadail or Mymensingh Sadar (Central), Bhaluka, and Gaffargaon, of the Mymensingh district.

The study has been carefully designed to ensure that all of the adolescent girls between the ages of 10–17 years meet the study inclusion criteria: non-smoking, not married, not pregnant, not breastfeeding, and generally healthy. Adolescent girls who choose not to participate, are ill during recruitment, or are known to have infectious disease will be excluded. Standard Protocol Items: Recommendations for Intervention Trials (SPIRIT) 2013 (Fig. 1) will be used to report the study [17]. Table 1 presents a summary of the trial according to the World Health Organization (WHO) Trial Registration Minimal Data Set as described by Moja et al. [18].

**Fig. 1 Fig1:**
[figure not shown]
Flow chart of iron-fortified lentil feeding trial

**Table 1 Tab1:** Summary of the trial according to the World Health Organization (WHO) trial registration minimal data set

	Data	Information
1	Trial identification number (unique trial number)	ClinicalTrials.gov NCT03516734
2	Trial registration date	24 May 2018
3	Secondary IDs	Bio# 17–177 (ERC, University of Saskatchewan) IRB#1139116–2 (IRB, Marywood University) BMRC/NREC/2016–2019/455 (Bangladesh Medical and Research Council)
4	Funding source(s)	Global Institute for Food Security, University of Saskatchewan, Canada; Nutrition International, Canada
5	Primary Sponsor	[name] (University of Saskatchewan)
6	Secondary Sponsor	[name] (University of Saskatchewan)
7	Responsible contact person (contact for public queries)	[name], College of Pharmacy and Nutrition, University of Saskatchewan, [name], Saskatchewan, Canada. [contact]
8	Research contact person (contact for scientific queries)	[name], RDN, LDN, Nutrition, Athletic Training and Exercise Science, Department of Nutrition and Dietetics, Marywood University, [name], USA. [contact]
9	Title of the study (brief title)	Iron-fortified lentils to improve iron (Fe) status among adolescent girls in Bangladesh
10	Official scientific title of the study	Iron-fortified lentils to improve iron (Fe) status among adolescent girls in Bangladesh - study protocol for a double-blind randomized controlled trial.
11	Research ethics review and country of recruitment	• Ethical approved received from 1. University of Saskatchewan REB (Ref: Bio# 17–177) 2. Marywood University IRB (Ref: IRB#1139116–2) 3. Bangladesh Medical and Research Council. (Ref: BMRC/NREC/2016–2019/455) • Country of recruitment: Bangladesh
12	Health condition studied	Iron deficiency
13	Intervention	Fe-fortified lentils
14	Key inclusion and exclusion criteria	Inclusion criteria: adolescent girls aged 10–17 years, non-smoking, not pregnant, not breastfeeding, and generally healthy Exclusion criteria: adolescent girls with active illness during recruitment, or with known infectious disease
15	Study type	Double-blind, community-based, cluster-randomized controlled trial
16	Trial start date (anticipated)	Mid-September 2018
17	Target sample size (total)	1260 adolescent girls.
18	Recruitment status	Not yet recruiting
19	Primary outcome	Serum ferritin level and cognitive performance of the adolescent girls
20	Key secondary outcomes	1. Growth (height, body weight, triceps skinfolds, mid-upper arm circumference) of non-pregnant adolescent girls in Bangladesh 2. Blood hemoglobin level of non-pregnant adolescent girls in Bangladesh

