Venous blood samples will be collected by a trained phlebotomist; ~ 10 ml of blood will be collected from each participant using lithium heparinized vacutainers following an aseptic procedure and using a disposable syringe and needle. Vacutainers will be transported within 12 h of collection to the International Center for Diarrhoeal Disease Research, Bangladesh (ICDDRB), based in Dhaka. In the state-of-the-art facility laboratory, the serum will be separated and stored at a temperature of 2–8 °C and then analyzed. The blood collection per participant will take about 10 min. We propose to measure complete blood count (CBC), which includes the following: erythrocyte sedimentation rate (ESR), hemoglobin (Hb), hematocrit, packed cell volume (PCV), mean corpuscular hemoglobin (MCH); mean corpuscular volume (MCV) ; mean corpuscular hemoglobin concentration (MCHC), red blood cells (RBC), white blood cells (WBC) total count, differential count, platelet count; sFer, soluble transferrin receptor (sTfR), C-reactive protein (CRP), and blood ABO typing.

Five common measures of attentional (three attention tasks) and mnemonic functioning (two memory tasks) will be used to assess the use of cortical systems and circuits that have been documented to have some dependence on Fe status, based on the literature on either human or animal studies. These measures and tasks have been used extensively in human experiments, and have each been described previously [13, 14]. These computerized assessments will be used to measure attention and visual memory, as used in previous biofortification feeding trials in similar target populations [21–24]. Briefly, all tasks will be undertaken by pre-installed DMDX software (developed by the University of Arizona) and will include detailed instructions and practice tests [25]. This computer-based application will be administered by trained local research assistants.

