The simple reaction time (SRT) task provides an estimate of the speed of the simplest possible behavioral response to a visual stimulus and requires a participant to press a button in response to the onset of the task stimulus [26]. The go/no-go (GNG) task provides an estimate of the efficiency of sustained attention and the speed of simple attentional capture without the need to filter information from any immediately competing stimuli [26]. It requires a participant to press a button in response to the presentation of an infrequent stimulus (presented on 20% of the trials) and to withhold a response to a frequent stimulus (presented on 80% of the trials). The attentional network task (ANT) is a modified flanker task that provides an estimate of the effectiveness of three distinct components of attention [27]. In each trial, a participant will be presented with either an informative or an uninformative cue and will be required to press a button to indicate whether an arrow in the center pointed to the left or right while attempting to disregard flanking elements. The cued recognition task (CRT) is a modified version of a classic, visual recognition, memory task that estimates the speed, accuracy, and efficiency of recognition based on short-duration visual memory [28, 29]. Participants will be presented with a set of pictures of common, easily named objects, after which an equal number of previously seen and new items will be presented, and participants will be required to indicate whether each item was in the original set or is new. The Sternberg memory search (SMS) task estimates the speed and accuracy with which immediate visual memory can be searched [30]. In each trial, participants will be first shown a set of 1, 3, or 6 simple graphical symbols to remember, then a test stimulus will be presented, and the participant will indicate whether she remembers the test stimulus from the previous set of symbols. It would take around 45 min per participant.

Data on how much cooked lentil was served to each adolescent girl and how much remained uneaten by each girl will be collected on a daily basis by the research assistants. This information will be used to determine the actual amount of cooked lentil consumed by the adolescents.

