#### Cognitive performance

Participants’ attention, and memory (number of correct responses and time (seconds and milliseconds)) will be measured using DMDX software.

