### Statistical analysis

Baseline characteristics, i.e., all covariates, will be examined for group comparability to determine if randomization was successful. An intent-to-treat approach will be followed in the analyses of outcome data at the end of the intervention. Outcome variables such as sFer, and Hb will be set using different cutoffs from the National Micronutrients Status Survey 2011–12 [2]. Data will be analyzed with and without adjustment for baseline characteristics. Group means for changes in biochemical variables, anthropometric measures, and post-intervention morbidity rates will be compared using mixed models (with cluster as the random effect), with the respective baseline values serving as the primary covariate. After these preliminary analyses, key outcome variables (sFer and the cognitive performance of the adolescent girls) will be re-examined and additional covariates will be included in the model such as factors that differed by intervention arm, i.e., age, socio-economics, anthropometrics, food security, drinking safe water, hygiene practices etc.). Additional continuous outcome variables will also be examined using a generalized linear model (GLM), adjusted for confounding factors such as age, socio-economics, anthropometrics, food security, drinking safe water, hygiene practices, etc. Categorical variables will be compared using the chi-square test or logistic regression adjusted for possible confounding factors. With the assumption that data will be missing at random (MAR), multiple imputation or likelihood-based mixed models will be used for analysis, after complete case analysis and examination of missing data within and between treatment groups. All outcome variables will be examined for normality, and outliers will be identified. Data collected from adolescent girls suffering from severe Fe deficiency and/or acute infection will participate in all aspects of the study but results of supplementation in this group will be analyzed separately. All analyses will be performed using SPSS for Windows PAWS version 25. A *p* value <0.05 will be considered statistically significant for all main effects.

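### Ferritin and an undefined multi-task 'cognitive performance' share the primary outcome under a flat 0.05 rule, with no testing order or error control between them

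*Protocol article*

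**What the plan says.** Table 1, row 19, names the primary outcome as "Serum ferritin level and cognitive performance of the adolescent girls". The Statistical analysis section pairs the same two domains: "key outcome variables (sFer and the cognitive performance of the adolescent girls) will be re-examined" with further covariates. Its closing rule is that a p "value <0.05 will be considered statistically significant for all main effects".

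Cognition is not one variable. Under Data collection tools and technique, "Five common measures of attentional (three attention tasks) and mnemonic functioning (two memory tasks) will be used". Under Cognitive performance, participants' "attention, and memory (number of correct responses and time (seconds and milliseconds)) will be measured using DMDX software". The task descriptions differ in what they yield: simple reaction time "provides an estimate of the speed of the simplest possible behavioral response to a visual stimulus", while the attentional network task "provides an estimate of the effectiveness of three distinct components of attention". No task, score or composite is singled out.

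Trial objectives opens with "The primary objective of the study is to determine the effectiveness of an Fe-fortified lentil-based dietary intervention" on iron status. Cognition enters there through the hypothesis, as a consequence of better iron status. The same section ranks the arm comparisons: fortified versus unfortified lentils is primary, and fortified versus usual intake is secondary. The sample size section plans cognition as a single two-tailed test at 5%.

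**The concern.** The article fixes two things that do not fit together: a primary outcome with several measurable components, and a threshold of 0.05 for each effect taken separately. Followed as written, the plan offers several routes to a significant primary finding at the full 5% each, and nothing says how they combine into a conclusion. The single 5% test assumed in the cognitive sample size has no matching single endpoint.

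The results are meant to support large-scale production of the fortified product. A cognitive benefit claimed from whichever task score happened to cross 0.05 could enter that case without real support. The trial status is not yet recruiting, so the rule can be settled before any data exist.

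**Working it through.** The article states no overall error rate, so there is no figure of its own to reproduce. Its only error figure is 0.05 per main effect.

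**Inputs from the article**
- Alpha 0.05 per test (Statistical analysis).
- One primary arm comparison, fortified versus unfortified (Trial objectives).
- Ferritin: one test.
- Cognition: five tasks, recorded as number correct and time. Two scores per task would give ten. That count is approximate, because simple reaction time is described only as speed and the attentional network task has three components.

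**Assumptions, not in the article**
- The correlation among cognitive test statistics, taken as equal for all pairs and varied from 0 to 0.9.
- Ferritin and cognitive test statistics uncorrelated.
- No true effect on any outcome, unless stated otherwise.

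**If any one success counts**

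For k independent tests, the chance of at least one p below 0.05 is 1 − 0.95^k:
- ferritin plus one cognitive endpoint, k = 2: 1 − 0.95² = 9.75%
- ferritin plus one score per task, k = 6: 1 − 0.95⁶ = 26.5%
- ferritin plus ten cognitive scores, k = 11: 1 − 0.95¹¹ = 43.1%

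Correlated scores lower these figures. A simulation of 400,000 draws of normal test statistics gives the remaining rows:

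| Correlation among cognitive scores | Ferritin + 5 scores | Ferritin + 10 scores | Any of 5 cognitive scores | Any of 10 cognitive scores |
|---|---|---|---|---|
| 0 (formula) | 26% | 43% | 23% | 40% |
| 0.3 | 25% | 38% | 21% | 35% |
| 0.5 | 22% | 32% | 18% | 29% |
| 0.7 | 19% | 25% | 15% | 21% |
| 0.9 | 15% | 17% | 10% | 13% |

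**If both domains must succeed**

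Under no effect at all, the false-positive rate is 0.05 times the chance of any significant cognitive score. The largest case, ten independent scores, gives 0.05 × 0.401 = 2.0%. Correlation between ferritin and cognition could raise this, but never above the 5% of the ferritin test itself.

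If ferritin truly improves and cognition does not, the ferritin condition is usually met and gives little protection. The false cognitive claim then has nearly the chance shown in the last two columns: about 10% (five scores, correlation 0.9) to 40% (ten independent scores).

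**The case against.** The strongest reply is that the article never says one success is enough. It joins the two domains with 'and', which could mean that both are required, and the overall rate under no effect would then be low. This stands: every any-one-counts percentage is conditional. But the article does not state a both-must-succeed rule either, and such a rule would not protect the cognitive claim when ferritin responds.

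A second reply is that scoring, composites and multiplicity procedures are commonly left to an analysis plan that is not shown. This is fair for the choice of score. It does not cover the two-domain primary outcome and the flat 0.05 rule, both of which the article itself states; a later plan that controlled error would have to depart from that rule.

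Third, the number of scores is not given, and scores from one battery in the same girls are likely to be correlated. The sizing of cognition as one test is also compatible with one intended endpoint. So 43% is illustrative, and 9.75% is the figure if a single endpoint was meant.

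Two stronger readings are tempting and not supported:
- A reader might add the usual-intake comparison, count 22 tests and arrive at 1 − 0.95²² = 68%. Trial objectives makes that comparison secondary, so it is outside the primary family. The inflation comes from outcomes, not arms.
- A reader might see a flat contradiction between Table 1 and the objectives. The hypothesis and the Study design section both include cognition, and both outcomes are sized. The standing of cognition is uneven across sections, but two primary outcomes are a possible choice.

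**Conclusion.** The point holds in a conditional form. The article names a two-domain primary outcome, leaves the cognitive part without a defined endpoint, and tests everything at 0.05 with no order or alpha control. If any one success counts, the false-positive chance in the primary comparison is 9.75% at the least under the assumption that ferritin and the cognitive endpoint are uncorrelated. It is about 15% to 26% with one score per task and about 17% to 43% with roughly ten scores, over correlations from 0.9 down to 0. If both must succeed, the overall rate is about 2% or less, yet a false cognitive claim alongside a true ferritin effect still has about a 10% to 40% chance with five to ten scores.

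That the rule is unstated and the error uncontrolled is clear from the text. The exact size is not, because it depends on a success rule, a number of scores and correlations that the article does not give.

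**What to change.** Replace the blanket 0.05 sentence with a stated order for fortified versus unfortified lentils:
1. Endline serum ferritin at two-sided 5%.
2. Only if that is significant, cognition, either as one pre-named composite at 5% or as one named score per task with Holm adjustment over the five.

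The remaining task scores become supportive. Fortified versus usual intake stays secondary, as already stated. Align Table 1 with the objectives, and update the registry entry too if it carries the same wording.

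**Cost**
- Ferritin power is unchanged, since ferritin keeps the full 5%.
- No confirmatory cognitive claim is possible if ferritin is not significant. At the planned 80% power, that happens 20% of the time even when the assumed ferritin effect is real.
- Under Holm, the smallest of the five cognitive p values must be below 0.05/5 = 0.01. With 80 analysed per group, design effect 1 + 4 × 0.025 = 1.1, and the article's 70% effect size read as 0.70 SD (an assumption), 0.70/√(2 × 1.1/80) = 4.22. Power for one score at 0.01 is Φ(4.22 − 2.58), about 95%, against 98.8% at 0.05.

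**Alternative.** Keep two primary outcomes, with one named cognitive endpoint and alpha of 0.025 each. This preserves a cognitive claim when ferritin misses, but costs ferritin power. With all 420 per arm analysed (26.25 per club), the effective number is 420/(1 + 25.25 × 0.025) = 257 per arm, and 5/(20 × √(2/257)) = 2.84. Power falls from Φ(2.84 − 1.96), about 81%, to Φ(2.84 − 2.24), about 72%. The fixed order is therefore cheaper for ferritin and follows the causal chain in the hypothesis.
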